#### Program Approach

The parent program will be based on several key theoretical approaches that have been shown to be effective in supporting parents and/or in addressing a range of psychosocial difficulties.

First, the program will adopt strategies from a Cognitive Behavioural Psychology (CBT) approach. In particular, Social Learning Theory (also known as Behavioural Family Intervention or Parent Management Training), is an approach that has been applied extensively and effectively in the parenting field. This theory will inform both the learning processes and the program content. Social Learning Theory approaches utilise behaviour management training, modelling, and generalisation and maintenance strategies, such as in session and between session practice, to assist parents to achieve changes in their children's and their own behaviour. Positive outcomes include reductions in child internalising and externalising behaviour problems, increases in parental confidence and effectiveness, improvements in the psychosocial health of parents (including anxiety, depression and self esteem) and development of skills for improving parenting practices and improving the parent-child relationship quality (Johnson, Franklin, Hall, & Prieto, 2000; Sanders, Markie-Dadds, & Turner, 2003; Webster-Stratton & Hammond, 1997). In relation to SCILs, interventions that have incorporated CBT strategies such as problem solving have been demonstrated to be the most effective to date (A. Kazak et al., 1998; O. J. Z. Sahler et al., 2002). Additionally in the area of SCILs, such as acquired brain injury, parenting programs targeting difficult child behaviours are showing some promise (Feeney & Ylviaksaker, 1995; Slifer et al., 1996).

In addition, the intervention will also incorporate strategies from a contextual-behavioural psychology approach. This approach also has its origins in the field of Cognitive Behavioural Psychology, is relatively new and has increasing levels of evidence for its effectiveness in addressing a range of psychological difficulties, including, depression and anxiety in adults and children, chronic health difficulties such as diabetes and pain and substance addictions. Contextual behavioural approaches aim to increase psychological flexibility of participants via increases in the use of acceptance and mindfulness strategies, thereby assisting them to deal with their cognitions and emotions in more helpful ways resulting in reductions in physical and mental health difficulties and other psycho-social conditions (Hayes, Luoma, Bond, Masuda, & Lillis, 2006). Some researchers have suggested that these approaches may extend the benefits of traditional Social Learning Theory based parenting interventions (Dumas, 2005; Greco & Eifert, 2004) by assisting parents to develop

strategies for dealing with thoughts and emotions that may act as barriers to effective parenting during times of distress. The approach has only begun to be used in the areas of parenting and trauma, however, the objectives of the approach and the targets of change are consistent with Kazak's PMTSM in that they aim to target an individual's appraisal of their thoughts and emotions, and may therefore help parents to reduce the level of distress they experience in relation to the events surrounding their child's illness/injury.

#### Program Adherence

The parent intervention groups will be facilitated by five mental health professionals (e.g., psychologists and therapists). The intervention is highly manualised and includes verbatim examples instructing facilitators on how to introduce key concepts during each session. Each session will contain a schedule outlining the strategies that must be covered during the session. To further ensure treatment fidelity the following strategies will be employed:

- Each session will contain an adherence checklist and facilitators are responsible for adhering to the checklist and completing it after each session.
- All facilitators will undergo extensive training in the delivery of the intervention. The training will include observing the sessions being delivered by the leading clinician, role playing session content and receiving feedback regarding the delivery of session content.
- Audio of the sessions will be recorded using the Google Hangouts program. The audio files will be stored on a password and firewall protected computer (on the hard drive) which can only be accessed by members of the research team. The taped sessions will be used to evaluate how the facilitators' perform in the session – e.g., their adherence to the program material, their clinical delivery skills etc. A team member will code aspects of the program to ensure treatment fidelity and to give an indication of inter-rater reliability.

#### Treatment Arms

##### 1. Take A Breath (TAB)

TAB will aim to provide parents with practical strategies and approaches to better cope with the traumatic experience of having a seriously ill/injured child. The intervention will incorporate strategies that seek to directly target the parents' perceptions of the events surrounding their child's illness. The intervention will use a range of metaphors and experiential activities based on the evidence-based approaches described above, to assist parents to explore their current context and how best to cope as an individual, a parent and a family during and beyond their child's diagnosis, treatment and recovery. Participants will be encouraged to practice ideas and strategies from the program in between each session. Each session will involve reflection of past session content and parent attempts to implement program strategies.

TAB will incorporate strategies that assist parents to:

- Deal with the negative thoughts and emotions (stress, worry, anger, sadness) that result from having a child with a SCII
- Maintain their parenting role in the face of their child's SCII and their own emotional responses
- Develop plans for handling the disruptions to family relationships, roles and activities
- Maintain/develop supportive social connections/networks

2. Waitlist control

The waitlist control group will receive standard clinical care within the hospital, including access to nurses, consultants, social workers, and psychologists. After completion of the pre and post intervention questionnaire as the comparison group, the waitlist group will then be offered the TAB intervention if they are interested.

## 6. SUBJECT ENROLLMENT FOR SCREENING OF PARENTS

### 6.1 Recruitment

The details of the project and the study objectives will be provided to key staff from the RCH Departments via a face to face briefing. These staff will be asked to promote the study and the parent program to new families (within four weeks of diagnosis) attending the department for treatment. A screening process will be used to determine eligibility for the parent intervention program.

Participants will be parents of children during their first presentation for a diagnosis of cancer, cardiac disease, or who have been admitted to hospital in the PICU department. Participants will primarily be parents of children receiving inpatient services, however, in some instances parents may be seeking services for their child on an outpatient basis.

Participants will be asked to consent to participate in Screening in order to determine their eligibility into the RCT trial (parent intervention groups), to allow the research team to access their child's medical records for relevant medical and demographic information, and to consent to be recontacted in 3-6 months' time to be invited to participate in the RCT.

The Screening Questionnaire involves the completion of the ASDS on a single occasion within four weeks of their child's diagnosis (T1) along with the Demographic Questions. Parents who report pre-existing psychological conditions and/or other trauma/death will be considered ineligible for the RCT. The information obtained from the Screening Questionnaire, specifically the results from the ASDS, will provide key inclusion criteria regarding eligibility into the RCT. Parents **must score greater than or equal to 9 on items 1 to 5 (dissociation items) AND greater than or equal to 28 on items 6 through to 19 (combined items from hypervigilance, re-experiencing and avoidance subscales)** using the cluster scoring method. The ASDS will also provide important acute distress data on parents psychosocial functioning within four weeks of their child's diagnosis/surgery/admission and the demographic information gathered will ask about marital status, employment etc.

### Eligibility Criteria

#### Inclusion Criteria

To be eligible to participate parents must meet all of the following criteria:

1. Parents must have a child aged between zero and eighteen years during their first presentation treatment for a SCII (cancer, cardiac disease or who have been admitted to hospital in the PICU department)
  - Cardiac – child required surgery within the 1st month of life. This decision was made following consultation with the Head of Cardiology who recommended that we target this group of parents as they are more likely to be traumatised compared to other parents of children with cardiac disease.
  - Cancer – all cancer types
  - PICU – child's stay at PICU must be greater than or equal to 48 hours
2. Parents may be male or female

- 313 3. Both mothers and fathers can participate together or individually, however the  
314 eligible parent must take part
- 315 4. Parents must have an active and current parenting role with the child (defined  
316 as the person(s) who perceives that they have an active parenting role)
- 317 5. Parents must be able to comply with the study intervention and assessment  
318 protocols. This will be determined by the researcher during registration contact  
319 with the parent
- 320 6. Parents may have multiple children diagnosed with an SCII
- 321 7. Parents must be over 18 years

322  
323

#### **6.2.2 Exclusion Criteria**

- 324 1. Parent has experienced other major trauma (e.g., death of child, partner or  
325 other loved one in two months prior to child's diagnosis)
- 326 2. Parent has a pre-existing psychological condition
- 327 3. Parent does not have current access to children
- 328 4. Parent has limited spoken English and/or literacy. This will be determined by the  
329 researcher during initial consultations with the parent
- 330 5. Child is not expected to live longer than 6 months

### **331 SUBJECT ENROLLMENT AND RANDOMISATION FOR RCT**

#### **332 Recruitment**

333

334 Families determined as eligible from the Screening questionnaire (ASDS cluster scoring: a  
335 score of 9 or above on items 1 to 5 AND a score of 28 or above on items 6 to 19) will be  
336 invited to participate in the parent intervention program.

- 337 a. During the telephone call to invite parents to take part in the RCT the researcher  
338 will describe in full the requirements of participation in the efficacy trial. Parents  
339 will be sent a plain language statement and consent form (see Appendix 4: PICF  
340 – Parent Intervention Group – Parent Version) and a flyer detailing information  
341 about the TAB program. Parents will also be given the opportunity to ask  
342 questions. Parents will be asked if they would prefer the PICF to be sent via the  
343 mail or online. For those parents who have chosen to receive the PICF online,  
344 they will be provided with the option of having a copy of the PICF either mailed  
345 or emailed to them.
- 346 b. If neither parent is interested at that time, contact will cease unless the family  
347 indicates they would like time to consider the study.
- 348 c. If a parent is interested in participating they will be asked to sign and return the  
349 consent form to the Research Team in the provided reply paid envelope. For  
350 those parents who have selected to consent online, they can either return the  
351 signed PICF via email Parent and Researcher consent may therefore not be  
352 dated the same.
- 353 d. Upon receipt of signed consent forms, parents will be enrolled into the study  
354 and then randomly allocated to one of the two treatment arms.
- 355 e. If a family verbally consents to continue their participation when called, this  
356 verbal consent will be noted in the trial database. At this point, the parents will  
357 be enrolled into the study and then randomly allocated to one of the two  
358 treatment arms. The researcher will again encourage the participating parent to

return written or online consent. If a parent requires the consent form to be mailed out again, or if an email consent form is preferred, then the form will be sent to the family once more, in another attempt to obtain written consent. If we again have difficulty obtaining formal written or online consent, a second verbal consent will be obtained over the phone prior to questionnaires being sent out and participation in the program commences. During this same phone call, a member of the research team will determine days and times that best suit the parent for attending a parent program and schedule them into a group. Parents allocated to the W-L arm will be advised when to expect the first set of questionnaires and advised of the approximate starting month for their participation in a group (following the completion of their post questionnaire).

- f. Pre-assessment measures will be distributed two weeks prior to the commencement of TAB group sessions to parents enrolled in the two treatment arms. Pre-assessment measures must be completed by parents prior to the commencement of the parent program. Parents have the choice to complete the questionnaires online or via paper/pen format.
- g. Any pre-assessment measures not returned/completed prior to the commencement of the parent program will be followed up. Parents allocated to the W-L arm will be followed up individually via their preferred method of contact. For those parents within the W-L arm that have failed to return written consent forms, another consent form will be sent with these pre-questionnaires, and they will be encouraged to return the signed consent forms when they return the pre-assessment measures.

Parents may choose to withdraw permission to participate at any time and request removal of their information from the database.

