#### 7.4 Blinding Arrangements

Research team members responsible for recruiting families to the study or delivering the TAB intervention to families will be blind to the randomisation list. No researcher involved with recruitment or clinical delivery will have access to the randomisation list, thereby ensuring they are blind to client allocation and ensuring the randomness of allocation. A research officer, not involved in either the recruitment process or clinical delivery, will manage the randomisation list. When a consent form is received the research assistant responsible for recruitment will contact the research officer to have the participant placed on the randomisation list for the correct department using their subject identification code.

The research assistant will be informed of the allocation and will then contact the parent to discuss the allocation and plan their enrolment in a group as described above.

Researchers conducting the data analysis will be blind to participant identity and allocation. Analysis will be conducted on re-identifiable data only. A research assistant not responsible for analysis will conduct a re-identification of participant if needed.

Participants will be partially blinded. That means that participating parents will know if they have been randomised to W-L or the parent intervention arm (TAB) once they have been advised whether they will receive the intervention immediately or in two-six months' time.

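### The T2 'pre' PCL-5 is collected after parents are told their arm, so it is not a pre-randomisation baseline, and parents lost before T2 cannot be imputed by the planned method

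*Protocol*

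**What the plan says.** All references are to the Protocol.

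- **Randomisation.** Under RCT Recruitment, item d reads "Upon receipt of signed consent forms, parents will be enrolled into the study", with random allocation next. Item e deals with parents who consent verbally by telephone: they too will "be enrolled into the study and then randomly allocated to one of the two" arms at that point. Randomisation Procedures places this typically three to four months after diagnosis.
- **Disclosure.** Section 7.4: "The research assistant will be informed of the allocation and will then contact the parent to discuss the allocation". The same section accepts that parents then know whether they start now or wait two to six months. Item e adds: "Parents allocated to the W-L arm will be advised when to expect the first set of questionnaires".
- **T2.** Item f: "Pre-assessment measures will be distributed two weeks prior to the commencement of TAB group sessions to parents enrolled in the two treatment arms". Section 8.2 sends T2 to wait-list parents at the same time as to the matching TAB group. Table 2 puts T2 at week 20.
- **Pre-randomisation data.** Section 6.1: "The Screening Questionnaire involves the completion of the ASDS on a single occasion", within four weeks of diagnosis (T1). No PCL-5 is taken then.
- **Analysis.** Section 11.3 compares mean outcomes between groups with GEE models at a point it labels T3. Table 2 calls the post assessment T4, and I read section 11.3 as meaning that assessment. No T2 covariate and no change score is named. Section 11.2 replaces missing post scores with the average post score of participants who have the same or the closest pre score.

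**The concern.** The primary outcome is self-reported. A parent who has just learned that help starts soon may answer the PCL-5 differently from one who has learned that it does not. If so, the T2 scores differ by arm because of allocation, and T2 is a post-randomisation variable. Sections 3.1 and 4.1 frame the question as improvement and as a comparison at pre and post, so an analyst could reasonably compute change from T2 or adjust for T2. Either analysis would carry the shift into the estimated effect.

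There is a second route. Some parents may leave after hearing their arm and before returning T2. Section 7.5.2 asks withdrawn participants for no further assessments, so these parents have neither a pre nor a post score. If such losses differ by arm, the intention-to-treat comparison is no longer of the groups as randomised.

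**Working it through.** The Protocol gives no figure on this point to reproduce. The check is of sequence first, then of size on stated assumptions.

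**1. Order of events.** Consent (signed, or a first verbal consent), then randomisation (items d, e), then discussion of the allocation (section 7.4), then T2 (item f, section 8.2). Matching T2 dates across arms equalises calendar time; it does not hide the arm.

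**2. Length of the gap.** Three to four months is about 13.0 to 17.4 weeks. If Table 2 counts weeks from diagnosis, T2 comes 20 − 17.4 = 2.6 to 20 − 13.0 = 7.0 weeks after randomisation.

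**3. Where T2 enters estimation.** It does not enter the GEE in section 11.3 as written. It enters the imputation in section 11.2, and it would enter any change-score or T2-adjusted analysis.

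**4. Size if T2 is used.** Let b be the between-arm shift in mean T2 caused by disclosure, and s the slope of T4 on T2. Neither is in the Protocol. Assume b = 1 to 3 points, s = 0.5 to 0.7, and no lasting effect of the reaction at T4.
- T2-adjusted: bias = s × b, from 0.5 × 1 = 0.5 to 0.7 × 3 = 2.1 points. Divided by the 6.0-point target, this is 8% to 35%.
- Change score: bias = b, 1 to 3 points, or 17% to 50% of the target.
- Observed post scores only: bias from the shift = 0.

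Effect on the type I error for b = 2, with the planned SD of 13.9 and 82 per arm, a T2–T4 correlation of 0.6, equal SDs and independent parents: the standard error of a difference in post means is 13.9 × √(2/82) = 2.17.
- Adjusted: bias 1.2, standard error 2.17 × √(1 − 0.36) = 1.74; two-sided error about 0.11 instead of 0.05.
- Change score: bias 2.0, standard error 2.17 × √(2 × 0.4) = 1.94; about 0.18.

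**5. Size through imputation.** Recruiting 184 to retain 2 × 82 = 164 implies attrition of 1 − 164/184 = 0.11. If closest matches are pooled across arms, the upper end is about 0.11 × 0.7 × 3 = 0.23 points, under 4% of 6.0. If matching is within arm, a uniform shift leaves the matches unchanged and adds nothing. Section 11.2 does not say which is meant.

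**6. Early loss.** With no pre score there is nothing to match on, so section 11.2 cannot supply a post score. As an illustration only: if one arm loses an extra 10% of parents, and those lost would have differed by 5 to 10 points from those who stay, that arm's post mean moves by 0.10 × 5 = 0.5 to 0.10 × 10 = 1.0 point.

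**The case against.** The strongest reply is that the stated analysis makes no use of T2. A reader might infer that the T2 shift biases the planned primary comparison. Section 11.3 does not support that, and the figures in step 4 apply only if someone analyses change or adjusts for T2. This stands, as does the small size of the imputation route.

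The slope-times-shift formula can also be challenged. Wait-list parents still know their arm at T4. If the reaction persists, adjusting for T2 might remove some reporting bias rather than add to it. This too stands, and it is why no direction can be given.

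A reader might also infer that consent is obtained improperly late. The text does not support that: every parent consents in writing or verbally before allocation. Item e provides that, if formal consent is still outstanding, "a second verbal consent will be obtained over the phone prior to questionnaires being sent out". That follows randomisation, but the Protocol does not say whether it comes before or after the parent hears the arm. Only the form re-sent to wait-list parents with T2 (item g) clearly follows disclosure. What remains is an inconsistency: item e randomises on verbal consent, while section 7.4 has a parent placed on the list when a consent form arrives.

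On early loss, there are partial safeguards. Outstanding T2 questionnaires are chased, dropout is tracked under CONSORT (section 12.1), and the screening score is compared between groups (section 11.3). The intention-to-treat set may be defined further in an analysis plan not seen here. None of this gives the closest-match method a score to match on.

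**Conclusion.** The sequence is plain from the text: T2 follows randomisation and disclosure and should not be treated as a pre-randomisation baseline. The harm is conditional. A comparison of observed post scores takes no bias from a T2 shift. A T2-adjusted analysis would be biased by 0.5 to 2.1 points and a change-score analysis by 1 to 3 points under the assumed shift and slope, in an unknown direction. Pooled closest-match imputation would add at most about 0.23 points under the same assumptions.

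The problem with early loss does not depend on those assumptions. As section 11.2 describes it, the intention-to-treat analysis cannot include parents lost between disclosure and T2. How many there will be, and whether the arms will differ, cannot be told from the Protocol.

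**What to change.** 1. Add the T1 ASDS score as a covariate in the T4 GEE model, and state that T2 is not a pre-randomisation baseline. Every eligible parent has this score before randomisation, so it costs nothing to collect. The eligibility cut-offs restrict its range and it is taken months earlier, so the gain in precision may be modest. It does not remove a T2 shift if T2 is also kept in the model.
2. Keep randomised parents without T2 in the intention-to-treat analysis by a method that needs no T2 score, such as multiple imputation from T1 ASDS, arm and department. Report losses before T2 by arm. The cost is a short change to section 11.2. The method still assumes that those variables account for the loss, which is why the report by arm is needed.
3. Where enrolment still allows, collect the PCL-5 before allocation is disclosed. This has a real cost: groups wait for at least five TAB parents (section 8.2), so the gap from that score to session 1 becomes longer and more variable. The section on the primary outcome measure already reports internal consistency in this study's own data, so it may be too late for this step; items 1 and 2 do not depend on it.
4. Reconcile item e of RCT Recruitment with section 7.4 on what triggers randomisation. This is a wording change only.

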### **8.3 Evaluation**

Assessment data will be collected from all participating parents. Additionally, data regarding the child's diagnosis and treatment will be extracted from the child's medical file.

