Details regarding the patients' illness including date of diagnosis, diagnosis type, number of visits to the Emergency Department (ED) and number of days of admission will also be collected for study participants (parents who have returned consent forms). This information will be obtained from departmental/hospital databases by requesting a medical record extraction from The RCH Patient Information System (IBA). Patient diagnoses will be described. Length of treatment will be calculated from date of diagnosis to date for parents' completion of questionnaires. A member of the RT will collect the record and store it in a secure filing cabinet at MCRI prior to returning it to medical records.

All audio files recorded during the delivery of the intervention will be stored on a password and firewall protected computer in a locked room and will contain audio from both practitioner and parents. They will also be securely shared with the team's clinical supervisor using the MCRI OwnCloud system.

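### After allocation, only wait-list parents are promised individual follow-up and a further consent form, and illness data are tied to a returned form, so baseline and illness data may go missing differently by arm

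*Protocol*

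**What the plan says.** All references are to the Protocol.

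**Consent and randomisation.** In the Recruitment part of the RCT enrolment section, item d randomises on a signed form. Item e ("If a family verbally consents to continue their participation when called") also enrols and randomises on verbal consent. It goes on to further encouragement to return the form, one re-sending of it and, if that fails, a second verbal consent before questionnaires go out. Item e names no arm.

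**Baseline.** Item f places T2 after allocation: "Pre-assessment measures will be distributed two weeks prior to the commencement of TAB group sessions to parents enrolled in the two treatment arms". Section 7.4 confirms that parents know their arm once they are told when they will receive the program.

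**Follow-up.** Item g opens with a rule for everyone: "Any pre-assessment measures not returned/completed prior to the commencement of the parent program will be followed up". It then turns to one arm: "Parents allocated to the W-L arm will be followed up individually via their preferred method of contact". The consent re-send is also for that arm: "For those parents within the W-L arm that have failed to return written consent forms, another consent form will be sent with these pre-questionnaires". No contact method and no matching consent mailing are given for TAB.

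**Illness data.** Section 12.1 says that date of diagnosis, diagnosis type, emergency department visits and days of admission "will also be collected for study participants (parents who have returned consent forms". Section 6.1 has parents consent at screening "to allow the research team to access their child's medical records for relevant medical and demographic information". Section 8.3 says only that "data regarding the child's diagnosis and treatment will be extracted from the child's medical file".

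**The concern.** Equal follow-up effort in both arms is a basic safeguard in a randomised comparison. It matters more here because parents know their arm and report their own outcomes. Item g writes an arm-specific procedure into the protocol, at a point when allocation is already known, for two things: return of the baseline questionnaire and return of the consent form. If 12.1 refers to the RCT consent form, the second of these also decides whose illness data are collected.

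Four uses of the data depend on them:

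- the comparison of the arms before intervention;
- the length-of-treatment variable in 12.1, which starts at date of diagnosis;
- the predictor and descriptive analyses in 11.3;
- the closest-match method in 11.2, which needs a pre-intervention score.

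If return differs by arm because the chasing differs, these analyses carry a gap that randomisation cannot balance. Baseline data not collected before the program starts cannot be recovered later.

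**Working it through.** The protocol gives no rate of unreturned T2 packs or consent forms, so there is no figure to reproduce. The check is a comparison of the text, followed by illustrations under stated assumptions.

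**1. What each arm is promised after allocation**

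| Step | TAB | Wait-list |
|---|---|---|
| Encouragement, one re-sent form, second verbal consent (item e) | yes, no arm named | yes, no arm named |
| Missing T2 followed up (item g, opening sentence) | yes | yes |
| Contact method for that follow-up | not stated | individual, by preferred method |
| Further consent form with the T2 pack | not stated | yes |
| Deadline (item f) | before the program, so before the parent's own session 1 | timing matched to a TAB group (8.2), no session to attend |

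The documented difference is one stated contact method and one extra mailing, both in the wait-list arm.

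**2. Who supplies illness data**

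- Section 6.1: record access is part of the screening consent, before randomisation.
- Items d and e: parents enter the RCT on written or verbal consent.
- Section 8.3: extraction from the medical file, with no restriction.
- Section 12.1: only parents with a returned form; which form is not said.

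If 12.1 means the screening form, the limit need not exclude a randomised parent. If it means the RCT form, it excludes parents who stay on verbal consent, and item g gives wait-list parents one more chance to leave that group. Illness group itself is known for everyone, because each department has its own randomisation list.

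**3. Which analyses are exposed**

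- Main comparison (11.3): a GEE of group means, at a time point labelled T3 and read here as post-intervention. It names no baseline or illness covariate, so a parent with a post score but no T2 stays in.
- Closest match (11.2): a missing post score is replaced by the average of participants with the same or nearest pre score. A parent lacking both scores cannot be matched. A parent with a post score but no T2 cannot serve as a donor.
- Baseline description, length of treatment and predictor analyses: directly exposed.

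A rough ceiling for the closest-match route uses the total of 184 in 7.6 and the sample-size section (section 4.3 words 184 as a per-arm figure). 184/2 = 92 per arm, against 82 required, leaves 92 − 82 = 10 per arm for attrition. If loss of post scores stays within that allowance, at most 10 parents per arm could lack both scores.

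**4. Illustration: illness data**

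Assume that 12.1 means the RCT form and that 20% of each arm still lack one after item e: 0.20 × 92 = 18.4 parents per arm. If half of the wait-list group return the extra form and no TAB parent does, illness data are missing for 18.4 × 0.5 = 9.2 wait-list parents and 18.4 TAB parents. If TAB parents return forms at the same rate by other routes, the difference is zero.

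**5. Illustration: an analysis restricted to parents with T2**

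Let *m* be the share not returning T2 and *d* the number of PCL-5 points by which non-returners exceed their arm's average. The returners' mean then falls by d × m/(1 − m), and the shift between arms is

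d × [m_TAB/(1 − m_TAB) − m_WL/(1 − m_WL)].

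| Non-return, TAB vs wait-list | d = 5 | d = 10 |
|---|---|---|
| 10% vs 5% (0.1111 − 0.0526 = 0.0585) | 0.29 | 0.58 |
| 15% vs 5% (0.1765 − 0.0526 = 0.1238) | 0.62 | 1.24 |

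Against the 6.0-point target this is 0.29/6.0 = 5% to 1.24/6.0 = 21%. Swapping the rates between arms, or the sign of *d*, reverses the sign. With equal rates and equal *d* in both arms the shift is zero. All these inputs are assumed.

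**The case against.** The strongest reply is that the text does not show wait-list parents being pursued harder overall. Item g's opening sentence covers both arms. The next sentence gives a method for the wait-list and does not say that TAB parents go without individual contact. Item e chases the consent form in both arms. TAB parents also have a fixed deadline at session 1 and are in touch with staff who are scheduling them, so T2 return could be better in TAB. All of this stands. It reduces the point to a possible difference of unknown direction.

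A reader might infer that TAB verbal consenters are offered a second verbal consent in place of a written form. Item e does not support that: the re-sent form and the second verbal consent apply to both arms.

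A reader might also take the 0.3 to 1.2 points above as bias in the main result towards TAB. The protocol does not support that either. The formula drops every parent without T2, whereas the GEE in 11.3 names no baseline covariate and keeps those who have a post score. The direction is also a product of the assumed rates.

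Finally, the restriction in 12.1 may be a deliberate consent safeguard. The consent forms are not among the documents, so it cannot be called unnecessary, and it cannot be promised that no further consent would be needed. That stands and limits the second part of the fix.

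What the reply does not remove is that item g writes down extra steps for one arm only after allocation, and that 12.1 is narrower than 6.1 and 8.3 while items d and e admit parents without a returned form.

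**Conclusion.** The point holds as a risk: baseline and illness data may go missing differently by arm. It does not hold as a prediction that they will, or that one arm in particular will lose more. Size and direction are unknown because no return rates are given.

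The exposure is to the baseline description, length of treatment, the predictor analyses, and closest-match imputation for parents who also lack the post score. That last group is at most about 10 per arm if post-score loss stays within the attrition allowance. The main comparison of post-intervention means is not directly shifted. The illness-data part further assumes that 12.1 refers to the RCT consent form; if it refers to the screening form, that part largely falls away and only the wording needs settling.

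This is a modest weakness, worth correcting because it is avoidable and cheap to remove.

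**What to change.** 1. **Item g.** Rewrite it so that unreturned T2 packs and unreturned consent forms are followed up in the same way in both arms: same contact method, same number of attempts, same re-sent form with the pre-questionnaires. The cost is a few extra contacts or mailings to TAB parents.

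2. **Section 12.1.** State which consent form is meant, and reconcile the sentence with 6.1, items d and e, and 8.3. Illness data should be collected for all randomised parents whose consent permits record access, including the screening consent if its wording extends to these items, and subject to a parent's right to have data removed. Collection should not depend on a step after randomisation that is pursued differently by arm. The cost is a check of the consent wording and a short amendment. Whether any parent would need to be asked again depends on forms not shown here.

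Neither change touches the intervention, the sample size or the endpoint.
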